**Fitbit Protocol:** The purpose of the Fitbit portion of the study is to assess whether cannabis abstinence impacts objective measures of sleep in school-aged adolescents and young adults. At Baseline, participants will receive a Fitbit 3 that is paired with a premade, de-identified account. At the first visit, participants will be instructed on how to use the device, including charging and syncing. Participants will then be instructed to wear the device at all times (except when charging the device), from Baseline (Visit 1) through Visit 12 (approximately 70 days after Baseline). Participants will be instructed to sync their device frequently throughout the study. At each visit, a member of study staff will also sync the Fitbit to the Fitbit app to pair the deidentified sleep and activity data to the pre-made de-identified account.

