exploratory analyses for hypotheses 1.1 – 2.2 looking at all 5 individual items for suicidal ideation. To examine the impact of participants who are versus are not receiving mental health treatment, we will conduct a set of exploratory analyses for hypothesis 1.1 – 2.2 including a binary indicator for receipt of mental health treatment as an additional covariate. Additionally, we will conduct exploratory analyses for sleep and circadian rhythms. Sleep, circadian, and physical activity exploratory Fitbit metrics include: *Sleep duration*: mean and standard deviation [StD]) over the main sleep period, the day, and 24hrs; short (<6 hrs) and long (>9hrs) mean nocturnal sleep duration; *Sleep fragmentation*: Mean and StD of 7-day sleep efficiency and wake after sleep onset; *Sleep timing placement*: Mean sleep onset, offset, and mid-point; categorized also as advanced (sleep onset <0900) and delayed (sleep onset >0200); *Sleep timing variability:* Across-day StD of sleep onset, inter-and intra-day stability; sleep offset, and sleep mid-point; relative activity- adjusted amplitude (Roberts et al., 2020); *Physical activity:* Overall activity, time spent walking, in moderate and physical activity. Timing of maximal physical activity will be used in analyses of rest-activity rhythm. Data will be processed in a customized data management environment that interfaces with Fitbit cloud servers. This platform provides secure data acquisition and management tools that facilitate remote data collection without the need to return devices for data extraction. Using an in-house algorithm that captures continuous heart rate sensor data at 1-5-sec intervals, we will calculate minutes of non-wear time (i.e., absence of a pulse for ≥60 secs), enabling us to determine compliance and distinguish between real and spurious sedentary time. Missing data will be handled using interpolation. Labeled sleep stage data will be retrieved at a granularity of 30s, activity counts at 60s, and the heart rate at 1s. Sleep-wake metrics will be generated using signals from accelerometry, heart rate, and heart rate variability processed by Fitbit’s proprietary, validated algorithm (Dillon et al., 2005). Valid sleep data will be defined as non-nap sleep durations >3 hr. Physical activity will be derived from daily step counts detected by Fitbit’s triaxial accelerometer, which agrees with direct observation, and will be reported as daily and intraday (per minute) step counts. Using step counts, we will calculate minutes spent doing sedentary, light, moderate, and vigorous activity. Metrics will be calculated for each 24-hour period, generating averages and within subject standard deviations (to assess within-subject variability).

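### The exploratory Fitbit sleep-timing categories overlap from 02:00 to 09:00 and leave no middle band, and the 3-hour validity rule screens nights on the outcome being measured

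*Protocol*

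**What the plan says.** The Exploratory analyses paragraph under Data analysis lists the Fitbit metrics. Under timing it names "Mean sleep onset, offset, and mid-point", then adds that these are "categorized also as advanced (sleep onset <0900) and delayed (sleep onset >0200"). The later paragraph headed Sleep & Circadian Rhythms (Exploratory) repeats these cut-offs. Neither place says a.m. or p.m., or where the sleep day begins.

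For duration, the listed metrics include the mean, the standard deviation and the categories "short (<6 hrs) and long (>9hrs) mean nocturnal sleep duration". The Exploratory analyses paragraph also sets a validity rule: "Valid sleep data will be defined as non-nap sleep durations >3 hr". Earlier in that paragraph, heart-rate data are used so that "we will calculate minutes of non-wear time (i.e., absence of a pulse for ≥60 secs"), and the next sentence reads "Missing data will be handled using interpolation".

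The Fitbit Protocol text under Platforms for Data Collection gives the aim of the component: to "assess whether cannabis abstinence impacts objective measures of sleep in school-aged adolescents and young adults". The status is plain: "Additionally, we will conduct exploratory analyses for sleep and circadian rhythms".

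**The concern.** Advanced and delayed are opposite ends of one scale. A usable pair of cut-offs puts each onset in at most one of them and leaves ordinary bedtimes in neither. The printed pair appears to do the reverse. Because the error stands in both descriptions, the second does not correct the first. An analyst would have to guess the intended value, possibly after seeing the data.

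The 3-hour rule raises a separate question. Duration and its night-to-night SD are themselves outcomes. If a night is discarded because the measured duration is low, the lower tail of the outcome goes with it. If one group sleeps less, that group loses more nights and the contrast between groups shrinks.

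**Working it through.** The plan gives no numerical result for these rules, so there is no figure to reproduce. Two checks were made.

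**1. Timing cut-offs.** Inputs: advanced is onset before 09:00; delayed is onset after 02:00 (both Fitbit paragraphs). Each of the 1,440 clock minutes is classified by its distance from the start of the sleep day.

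| Sleep day starts at | Advanced only | Both | Delayed only | Neither |
|---|---|---|---|---|
| Midnight | 121 | 419 | 900 | 0 |
| Noon | 841 | 419 | 180 | 0 |

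The 419 minutes are 02:01 to 08:59 (539 − 121 + 1, in minutes after midnight). With a midnight start, 23:00 is delayed and 00:00 to 02:00 is advanced. With a noon start, 23:00 and everything else from 12:00 to 02:00 is advanced.

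The overlap disappears only if the sleep day starts between 02:00 and 09:00. With a 06:00 start, for example, advanced covers 06:00 to 08:59 (180 minutes), delayed covers 02:01 to 05:59 (239), and 1,021 minutes are in neither. But advanced then means falling asleep in the morning, which is not an early onset.

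Illustration only: if 0900 is a slip for 9 p.m., a noon start gives no overlap and an unlabelled band from 21:00 to 02:00 (301 minutes).

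**2. The 3-hour rule.** Input from the protocol: nights of 3 h or less are not valid. Assumed, because the protocol gives no sleep figures: nightly duration is normal with SD σ of 1.0, 1.5 or 2.0 h; the mean μ is 7 h, falling to 6.5, 6 or 5 h; invalid nights are simply dropped. With α = (3 − μ)/σ and λ = φ(α)/[1 − Φ(α)]:

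- share of nights dropped = Φ(α)
- mean of the remaining nights = μ + σλ
- SD of the remaining nights = σ√(1 + αλ − λ²)

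Example, σ = 2.0. At μ = 7, α = −2, λ = 0.0553 and the observed mean is 7.110. At μ = 5, α = −1, λ = 0.2876 and the observed mean is 5.575. The true fall of 2.0 h shows as 7.110 − 5.575 = 1.535 h, a loss of 1 − 1.535/2 = 23%. The observed SD at μ = 5 is 2√(1 − 0.2876 − 0.0827) = 1.59 h.

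| σ (h) | True fall (h) | Observed fall (h) | Attenuation | Dropped at 7 h | Dropped at lower mean |
|---|---|---|---|---|---|
| 1.0 | 0.5 | 0.499 | 0.2% | 0.0% | 0.0% |
| 1.0 | 1.0 | 0.996 | 0.4% | 0.0% | 0.1% |
| 1.0 | 2.0 | 1.945 | 3% | 0.0% | 2.3% |
| 1.5 | 0.5 | 0.477 | 5% | 0.4% | 1.0% |
| 1.5 | 1.0 | 0.934 | 7% | 0.4% | 2.3% |
| 1.5 | 2.0 | 1.746 | 13% | 0.4% | 9.1% |
| 2.0 | 0.5 | 0.431 | 14% | 2.3% | 4.0% |
| 2.0 | 1.0 | 0.833 | 17% | 2.3% | 6.7% |
| 2.0 | 2.0 | 1.535 | 23% | 2.3% | 15.9% |

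**The case against.** **The stakes are low.** The Fitbit metrics are exploratory, carry no numbered hypothesis and no power calculation, and lie outside the false-discovery control, which covers the six negative affect measures. The timing categories are an addition to continuous means that the bad cut-offs do not touch. The PSQI, scheduled at V1, V2 and V5 to V12, is a separate sleep measure to which the Fitbit rule does not apply. All of this stands and limits the weight of the point.

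**Day boundaries and clock arithmetic belong in an SAP or programming specification.** Silence on them is indeed no finding. But the cut-offs are not silence: they are a stated definition, printed twice, that does not work on either usual clock. The only boundary that separates the categories makes advanced a morning onset.

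**Voiding and interpolation are not linked.** A reader might infer that nights of 3 h or less are set to missing and then filled from neighbouring nights. The text does not say so. The interpolation sentence follows the non-wear text; the validity rule comes later with no missing-data rule attached. The Missing Data section also names multiple imputation and maximum likelihood. The bias above needs only the validity rule.

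**The effect is not hidden.** A reader might infer that the rule conceals sleep loss. Under the assumed ranges it attenuates it, often slightly, and sleep above 3 h still feeds the short-sleep category. The protocol states no direction for the effect of abstinence on sleep, so heavier loss of nights in CB-Abst is a possibility, not a prediction of the plan.

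**A minimum duration guards against mis-scored nights.** This is fair, but the planned non-wear detection can separate a worn short night from a device that was off the wrist.

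**Conclusion.** The point holds, as a correction to exploratory definitions. The timing categories are wrong as printed: on a midnight or noon clock, 419 minutes of the day fall in both opposite classes and none in neither. A 23:00 onset is mislabelled on both, but which label it gets depends on an anchor the protocol does not state; it would be wrong to say flatly that the plan calls it delayed. Because the categories attach to mean onset, what is misclassified is a participant or phase summary rather than a single night.

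The 3-hour rule is the lesser issue. It selects on the outcome, with attenuation from under 1% to about 23% and, at the extreme, an SD of 2.0 h read as 1.59 h. Those sizes rest on assumed normal nightly sleep, assumed SDs of 1 to 2 h, assumed falls of 0.5 to 2 h from a 7 h mean, and simple exclusion of invalid nights. The primary EMA outcomes and the power table are not affected.

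**What to change.** - In both Fitbit paragraphs, state that sleep timing is expressed on a noon-to-noon clock. Correct the advanced cut-off to the intended evening time so that a middle band exists. It may have been meant as 2100, but nothing in the protocol shows this and the sponsor must confirm the value. Settle it before the data are analysed.
- Define a valid night by worn time, using the heart-rate non-wear algorithm already planned. Keep worn nights of 3 h or less, at least in a sensitivity analysis.
- State that worn nights of 3 h or less are not filled by interpolation.

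The cost is wording and programming, with no new data collection. The small downside is that a few worn but mis-scored short nights stay in.

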At the end of 2 weeks, the app will automatically discontinue EMA surveys. Two 1-week EMA phases will occur during the randomized period (weeks 1 and 8 post randomization; Figure 1). Staff will re-train participants on the EMA app prior to each of these EMA phases. Staff members will monitor EMA compliance and will reach out proactively to participants failing to meet criteria. After the third and final EMA phase, participants will be reminded that they will no longer need the EMA app, and that they can delete it (see figure 1 study schema for illustration of EMA administration periods).

All EMA surveys, regardless of phase of the study, will consist of short, multiple-choice items with logic-branched follow-up items. Within each of these surveys, participants will be queried on social settings and activities, cannabis and other substance use, mood, and suicidal ideation. See sections below detailing our plan for data monitoring to ensure safety in the event of SI exacerbation.

**Actigraphy Component (Fitbit): P**articipants will participate in a study component that collects sleep and activity data via a Fitbit Inspire 3. Participants will wear the watch after enrollment at Visit 1 through the Visit 12 (approximately 70 days after enrollment). To enhance compliance, participants will be paid a $25 compliance bonus at each of the three EMA phases data is available for 16/24 hours of 80% of days within that phase.

| **Passive Parental Consent** | **Parental/student consent/assent** |  | **Cannabis users in CM discontinue cannabis use** |  |  |  |  |  |  |  |  |  |  |  |  |
| --- | --- | --- | --- | --- | --- | --- | --- | --- | --- | --- | --- | --- | --- | --- | --- |
|  | **V0** |  | **BL (V1)** | **V2** | **V3** | **V4** | **V5** | **V6** | **V7** | **V8** | **V9** | **V10** | **V11** | **V12** | **Exit interview** |
| Days since Baseline |  |  | 0 | 14 | 16 | 19 | 21 | 28 | 35 | 42 | 49 | 56 | 63 | 70 |  |
| Fitbit Inspire 3 |  |  | x | x | x | x | x | x | x | x | x | x | x | x |  |
| Phone Screener | x |  |  |  |  |  |  |  |  |  |  |  |  |  |  |
| EMA Assessments  (x indicates when EMA assessment phases begin) |  |  | x | x |  |  |  |  |  |  |  |  | x |  |  |
| *Substance Use Questionnaires* |  |  |  |  |  |  |  |  |  |  |  |  |  |  |  |
| AUDIT |  |  | x |  |  |  |  |  |  |  |  |  |  |  |  |
| CUDIT |  |  | x |  |  |  |  |  |  |  |  |  |  |  |  |
| CWS |  |  | x | x | x | x | x | x | x | x | x | x | x | x |  |

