Payments will be made using an escalating scale for abstinence reimbursements and on a consistent scale for EMA compliance (see Tables 1 & 2). The reimbursement schedule was informed by PI’s ongoing contingency management studies and has been effective in other populations (Worden et al., 2017). Maximum total earnings will be matched across group to not confound the potential effects of monetary payments and depressive symptoms and SI. Attendance payments paid via Advarra will be issued at the end of every in-person visit (when participants provide urine samples), abstinence payments will be made between visits when abstinence is biochemically confirmed, and EMA payments will be issued at the end of each of the three EMA phases.

| **Table 2: Max Overall Study Remuneration Schedule** | |
| --- | --- |
| **EMA Compliance Phase 1 (approximately 80%) completion** | $100 |
| **Or: EMA Compliance Phase 1 (approximately 50%) completion** | $25 |
| **Fitbit Compliance Phase 1 (66%) completion** | $25 |
| **EMA Compliance Phase 2 (approximately 80%) completion** | $100 |
| **Or: EMA Compliance Phase 2 (approximately 50%) completion** | $25 |
| **Fitbit Compliance Phase 2 (66%) completion** | $25 |
| **EMA Compliance Phase 3 (approximately 80%) completion** | $100 |
| **Or: EMA Compliance Phase 3 (approximately 50%) completion** | $25 |
| **Fitbit Compliance Phase 3 (66%) completion** | $25 |
| **Study Visits/ Abstinence** | $445 |
| **Overall Fitbit and EMA Bonus (completion across whole study)** | $50 |
| **Max Total Earnings $870** | |

Participants will earn either $100 for a compliance rate of approximately 80% or $25 for a compliance rate of approximately 50% across each of the three EMA phases and $25 for a Fitbit compliance rate of 66% across each of the three phases. Participants can earn an additional $50 if they achieve an overall compliance rate for both Fitbits and EMA phases across the entire study. Payments will be made at the study completion. If a Fitbit device is lost or not returned, 20% of the total earned for this portion of the study will be deducted.

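### The blanket interpolation rule for missing Fitbit data makes no exception for step counts, so unworn time can bias daily steps and active minutes in either direction

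*Protocol*

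**What the plan says.** All the analysis rules stand in one place: Protocol, Statistical Analysis, Data analysis, the exploratory analyses paragraph.

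- **Activity outcome.** Physical activity comes from Fitbit step counts, which "will be reported as daily and intraday (per minute) step counts". Sedentary, light, moderate and vigorous minutes are derived from those counts.
- **Unit of analysis.** "Metrics will be calculated for each 24-hour period, generating averages and within subject standard deviations".
- **Non-wear.** The plan detects it from heart-rate data: "we will calculate minutes of non-wear time (i.e., absence of a pulse for ≥60 secs"). Two uses are named: "enabling us to determine compliance and distinguish between real and spurious sedentary time".
- **Gaps.** "Missing data will be handled using interpolation". The type of interpolation, the signals it covers and the longest gap that may be filled are not stated.

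Two other places bear on how much is worn. Under Fitbit Protocol, participants are "instructed to wear the device at all times (except when charging the device"). Under Actigraphy Component (Fitbit), a bonus is paid at each EMA phase if "data is available for 16/24 hours of 80% of days within that phase"; the remuneration table lists this as "Fitbit Compliance Phase 1 (66%) completion".

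**The concern.** The plan computes the quantity needed to handle unworn time properly and then states a gap rule that does not use it. For a slowly changing signal, such as heart rate over a brief dropout, interpolation may be harmless. Per-minute step counts are different: they are mostly zeros broken by bouts of walking, so the minutes on either side of a gap say little about the hours inside it. A gap between two still minutes is filled with zeros, and a gap between two walking minutes is filled with walking.

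The invented values then enter the daily step total, the active minutes and the within-subject SDs. The device is worn for about 70 days and the third EMA phase comes at the end, so wear could plausibly change between phases. Wear could also differ between arms, for instance if the Aim 2 restriction to confirmed abstainers were carried over to the Fitbit data. In either case an artefact of wear could be read as an effect of abstinence on activity.

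**Working it through.** **Inputs from the protocol.** Metrics per 24 hours; per-minute step counts; interpolation with no stated method or gap limit; a bonus threshold of 16 of 24 hours on 80% of days.

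**Assumptions (not in the protocol).** One block of 8 hours (480 minutes) unworn; 16 waking hours (960 minutes, 07:00 to 23:00); steps spread evenly over waking time and none during sleep; linear interpolation of per-minute steps.

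**1. The protocol's own figure.** 16/24 = 66.7%, which agrees with the 66% in the remuneration table. It leaves 24 − 16 = 8 hours, used below only as a convenient scenario. A participant who just earns the bonus has at least 0.80 × 16/24 = 53% of phase hours recorded.

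**2. Totals without interpolation.** With u unworn waking hours out of W, the share of true steps captured is 1 − u/W. For W = 16:

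- u = 0: 1.00
- u = 4: 0.75
- u = 8: 0.50

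For u = 8, the share is 1 − 8/14 = 0.43 with 14 waking hours and 1 − 8/18 = 0.56 with 18.

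**3. Totals with linear interpolation, as the plan states.** Let T be the true daily steps, so the mean per waking minute is T/960. The expected fill is 480 × the average of the means at the two edges.

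| Device off | Edge means | Fill | Recorded | Sum |
|---|---|---|---|---|
| 15:00–23:00 (evening) | T/960 and 0 | 480 × T/1920 = 0.25T | 0.50T | 0.75T |
| 23:00–07:00 (overnight) | T/960 and T/960 | 480 × T/960 = 0.50T | 1.00T | 1.50T |
| 8 h inside the waking day | T/960 and T/960 | 0.50T | 0.50T | 1.00T |

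A minute-by-minute simulation with walking in short bouts (3,000 days per case) gave 0.75 for evening and 1.47 for overnight non-wear. Active minutes, counted there as 60 or more steps per minute, came to 0.64 and 1.47 of the truth. Shorter evening gaps gave 0.88 (4 h) and 0.94 (2 h) for steps.

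In the overnight case the uninterpolated total would have been right, and the stated remedy creates the error.

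**4. Within-subject SDs.** The fill on a given day depends on two edge minutes only. If both are at rest, an 8-hour gap adds 0 steps; if both are at 60 steps/min it adds 60 × 480 = 28,800. These are extremes, not expected sizes, but they show how the fill itself adds day-to-day spread.

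**5. Which denominator repairs it.** Scaling by all worn minutes does not:

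- evening: 0.50T × 1440/960 = 0.75T
- overnight: 1.00T × 1440/960 = 1.50T

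Scaling by waking worn minutes does, under the same assumptions:

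- evening: 0.50T × 960/480 = T
- overnight: 1.00T × 960/960 = T

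**The case against.** Several points on the other side are fair.

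- **The 16-of-24-hour figure is a payment criterion.** A reader might infer that the analysis tolerates 8 unworn hours a day. The documents do not say so: the threshold governs a bonus, participants are told to wear the device except when charging, and no days are admitted to or excluded from analysis on this basis. It is neither an allowance nor an upper limit. This stands, which is why 8 hours is only a scenario here.
- **Step counts need not simply track wear time.** A reader might infer that the metrics measure wear rather than activity. That fits only uninterpolated totals with the device off in waking hours. The plan interpolates, overnight non-wear costs almost no steps, and the error depends on timing and can have either sign. The stronger reading fails.
- **Non-wear is detected.** True, and it protects sedentary time in particular. But neither named use removes unworn minutes from the interpolation rule for steps.
- **Details may sit in an SAP that is not shown.** This holds for valid-day rules and gap limits, and their absence is not the complaint. The interpolation rule itself is stated in the protocol, without exception.
- **The sentence may have been meant for other signals.** Possibly; it stands among sentences on heart rate, sleep stages and activity counts. As worded it covers all of them.
- **The Missing Data section promises several methods for each analysis.** That could soften the rule, but it does not say that interpolated step data would be set aside.
- **Differential wear is not documented.** Correct. Confounding of arm or phase comparisons is conditional on it.

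**Conclusion.** The point holds in a limited form. The protocol detects non-wear and separately interpolates missing data, without linking the two for step-based metrics. Applied as written, this can bias daily steps, active minutes and their within-subject SDs. The direction depends on when the device is off: about 0.75 of true steps for 8 evening hours and about 1.5 for 8 overnight hours, with no expected bias when the gap has waking minutes at both edges and lies wholly in waking time. These sizes rest on even waking activity, a 16-hour waking day, a single 8-hour gap and linear interpolation, none of which the protocol specifies. Whether arm or phase comparisons suffer depends on wear differing, which is plausible but not shown. Physical activity is an exploratory outcome and no primary hypothesis is touched, so this is a low-priority improvement.

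**What to change.** Amend the exploratory analyses paragraph under Data analysis in four respects:

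1. Exempt step counts and sedentary, light, moderate and vigorous minutes from interpolation, and leave detected non-wear minutes missing for these metrics.
2. Analyse activity relative to waking wear time, either as a rate per waking wear hour or by modelling daily counts with log waking wear-minutes as an offset. Waking wear follows from the non-wear minutes and sleep-wake classification the plan already produces. All worn minutes should not be the denominator, for the reason shown in step 5 of the working.
3. Report wear time by arm and phase.
4. If a minimum-wear day is wanted, make it a sensitivity analysis with its own justification. Taking it from the bonus threshold would select days by adherence.

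The cost is a few sentences and no new data. The rate or offset has one weakness to state openly: it assumes that unworn waking time resembles worn waking time, which fails if the device is taken off selectively, for example for sport or rest.
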